#### Demographic Data

Participants will be asked to provide consent to share clinical data and will have demographic data collected at enrollment. This will include participant age, sex, relationship status, highest level of educational attainment, employment status, type of service (AMHS or CAMHS), and geographic service area (Community Health Organisation 1 & 2). Clinical data collected from the participant’s file will include details of current psychiatric diagnoses, current treatment plan (including medication if relevant), key clinician profession, and information in relation to previous suicidality to supplement participant self-report (suicidal ideation, nonsuicidal self-injurious behavior, and previous suicide attempt). Information regarding previous suicide risk or behavior is necessary to support patient safety and to inform factors that may be considered potential moderators or mediators in a full trial. A description of treatment received in both the TAU and the SafePlan conditions will be captured using the CSRI and clinical file data.

#### Data Sharing

At baseline, participants will be asked to consent to the researcher accessing their mental health clinical file; the researcher accessing details of the participant’s emergency contact or key clinician, consultant psychiatrist, and GP and sharing clinically important information with those individuals to maintain patient safety as necessary during the trial; and the collection of data post intervention and at 6-month follow-up.

Participants in the SafePlan condition will hold their own data on their device until they choose to show it to their mental health professional when they attend the clinic in person. Their data are not automatically shared or monitored, and this is communicated to participants both upon enrollment in the study and through the terms and conditions presented when downloading the app.

A separate participant information and consent form has been developed for use with mental health professionals who will partake in semistructured interviews focusing on the feasibility and acceptability of the intervention and study procedures. All interview data will be anonymized in the final report.

### Qualitative Interviews

Qualitative interviews will be conducted with patients (SafePlan group, n=12; control group, n=12) and clinicians (n=12) involved in delivering the intervention to assess the feasibility of the intervention and study procedures. The participants and their clinicians will be informed of the qualitative component of the trial during the consent process. Participants will be invited to attend a semistructured interview following the completion of the 8-week intervention. Semistructured interview topic guides will be used. Interviews will seek to better understand participants’ experience of the SafePlan intervention and of the study procedures and to identify barriers to engagement with the intervention. Researchers will also seek to interview participants in the control condition (n=12) to better understand their experiences of TAU, paper-based safety planning, potential contamination, and the acceptability of study procedures.

### Ethics Approval

This study was approved by the University Hospital Limerick Research Ethics Board in October 2021 (REC Ref: 055/2021). This study was preregistered through the Open Science Framework.

### Consent

The researcher will follow the SafePlan Standard Operating Procedure to take appropriate action to maintain participant safety throughout. In accordance with the HSE CAMHS Operational Guidelines [44] and local HSE policy and as stated in the study information sheet, this may include contacting the participant’s key clinician, consultant psychiatrist, GP, and emergency contact or contacting emergency services.

Participants will be identified by members of their mental health team and will be accessing treatment with an assigned key therapist for the entire duration of the intervention. Clinicians will identify potential participants for whom a safety plan is clinically indicated and will provide them with further information about the trial. Participants who wish to participate will be approached by the researcher, and informed consent will be obtained. In the case of those aged <18 years, assent will be required from the young person, and parental or legal guardian signed consent will be obtained before the person can proceed to enrolling in the study. All participants will be informed of their right to refuse to participate and their right to withdraw from the study.

In consenting to participate, the participants will also agree to the researcher accessing their clinical file. Information on the semistructured interviews and the fidelity assessment will also be provided, and consent to future contact for these purposes will be sought.

Data collected during the administration of the outcome measure will be shared with the participant’s key clinician to support participant safety. The researcher and any personnel involved in the study will receive standardized training in addressing suicidality in line with the Irish HSE National Office for Suicide Prevention Education and Training Plan 2021-2022 [45]. Baseline, outcome, and follow-up assessments will be conducted (unless otherwise required by the participant) in the participant’s mental health clinic and face-to-face to ensure optimum clinical support in situ. It is hoped that the semistructured interviews will provide further information on any potential adverse effects of data collection.

The SafePlan study will be conducted in accordance with the International Council for Harmonisation of Technical Requirements for Pharmaceuticals for Human Use Good Clinical Practice standards, which is an international minimum quality standard for the ethical and scientific conduct of clinical research [46]. Safety planning is an established suicide prevention intervention that has been found to reduce the recurrence of suicidal behaviors [15]. Therefore, although the information arising from that intervention will be recorded differently, participants across conditions will receive an evidence-based intervention that is considered good practice alongside TAU. One group will store this information on a paper-based safety plan template, and the other group will store the information on their SafePlan app.

### Fidelity Assessment

The MRC guidelines [37] on complex interventions strongly recommend the inclusion of fidelity assessment to explain discrepancies between expected and observed outcomes, to understand how context influences outcomes, to clarify causal mechanisms, and to provide insights to aid implementation.

Treatment fidelity assessment will include the following:

Documentation of key clinician’s behavior, including attendance at the SafePlan orientation and training session, completion and filing of paper-based safety plan (control condition), and development of an interactive safety plan and recording this plan using the SafePlan app (intervention condition).A checklist based on the 6 core steps outlined in the safety planning template by Brown and Stanley [13] will be used to assess the extent to which key components of safety planning are addressed by clinicians in both conditions.A sample (16/80, 20% approximately) of participant intervention sessions will be attended by the researcher, and the checklist will be completed to further assess the fidelity of the plan by Brown and Stanley [13].

### Health Economics

A cost-outcome description will be undertaken. Data on costs will be collected on resource use related to intervention delivery (staff costs, training, and intervention materials) and patient resource use in terms of the broader health service. The CSRI will be used at baseline, 8 weeks, and 6-month follow-up to capture information regarding the use of health and social care services, such as GP consultations, outpatient visits, use of hospital services for physical or mental health problems, and social worker contacts.

The cost of providing the intervention will be calculated based on the average time taken to carry out the intervention and the hourly cost of employing the mental health professional involved. The hourly employment rate of a mental health professional at the midpoint of the salary scale will be calculated based on the available health service salary scale [47]. This will be revised upwards to account for employer-related costs and overheads, based on guidance for conducting an economic analysis within the Irish health care system [48]. Following estimation of the cost of carrying out the intervention, net cost benefit and cost-benefit ratio for providing the service will be calculated.

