### Study Objectives

The study objectives are as follows: (1) examine the feasibility and acceptability of the SafePlan app as an adjunct to therapy for patients (aged 16-35 years) accessing secondary-level Irish mental health services and their clinicians; (2) assess the feasibility of the study procedures for both clinicians and patients within secondary-level mental health services; (3) determine the sample size required for a full randomized controlled trial (RCT) by collecting suicide outcome data at baseline, post intervention, and at 6-month follow-up; (4) determine whether the SafePlan app condition yields superior outcomes on the outcomes of suicidal ideation, suicidal behavior, and nonsuicidal self-injurious behavior at 6-month follow-up and post treatment when compared with the control condition; and (5) complete an economic analysis of the intervention.

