### Research Question

Is the SafePlan app, along with the proposed outcome measures, feasible and acceptable to patients aged 16-35 years at risk of suicide and their clinicians, in secondary-level mental health services in Ireland?

The feasibility and acceptability of using the following outcome measures in a full RCT will be assessed: the Beck Scale for Suicide Ideation (BSSI), C-SSRS, Coping Self-Efficacy Scale (CSES), Interpersonal Needs Questionnaire (INQ), and Client Service Receipt Inventory (CSRI) [38-42].

Data will be collected at baseline, post intervention, and at 6-month follow-up to determine whether the SafePlan app yielded superior outcomes on primary outcomes of suicidal ideation, suicidal behavior, and nonsuicidal self-injurious behavior when compared with the control group.

Participants: A total of 80 patients aged 16-35 years accessing secondary-level mental health services who present with current suicidal ideation, nonsuicidal self-injurious behavior, or a previous suicide attempt will be randomized to the SafePlan or control condition.Intervention: SafePlan is a safety planning mobile app informed by the paper-based SPI by Brown and Stanley [13]. Participants in the SafePlan condition will use the SafePlan app to record their safety plan in consultation with their mental health professional over an 8-week period as an adjunct to usual treatment.Comparison: The control group will receive treatment as usual (TAU) supplemented with the paper-based safety plan by Brown and Stanley [13] completed with their mental health professional.Outcome: The primary outcomes are feasibility outcomes and include the acceptability of the app to participants and clinicians, feasibility of delivery in this setting, recruitment, retention, and app use. Data collected on measures of suicidal ideation; suicidal behavior; and nonsuicidal self-injurious behavior at baseline, post intervention (8 weeks), and at 6-month follow-up will be used to compare changes in outcomes for the SafePlan condition relative to the control condition. A cost-outcome description will also be undertaken. Thematic analyses will be used to analyze the qualitative data gathered through semistructured interviews with patients and clinicians.

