## Methods

### Design

The SafePlan study is a pilot RCT of SafePlan, a mobile-based safety planning app. A parallel group randomized design will be used with 1:1 patient allocation to the 2 treatment arms. In the control condition, participants will receive TAU supplemented with a paper-based safety plan. In the intervention condition, participants will use the SafePlan app to record their safety plan in consultation with their mental health professional, in addition to routine treatment. In both conditions, participants will receive appropriate care through their mental health team for an elevated risk of suicide throughout the study. Quantitative data will be collected at baseline, post intervention (8 weeks), and at 6-month follow-up (from baseline), with an additional safety check assessment at 4 weeks in both conditions.

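### The health economics plan declares a cost-outcome description but commits to a net cost benefit and a cost-benefit ratio, with no monetary benefit defined and a cost basis that is not incremental between the arms

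*Protocol article*

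**What the plan says.** In the protocol article, Study Objectives lists as its fifth and last aim to "complete an economic analysis of the intervention", without naming a type of evaluation. The type is named elsewhere. The Research Question section says "A cost-outcome description will also be undertaken", the Abstract agrees, and the Health Economics section opens with "A cost-outcome description will be undertaken".

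Health Economics collects costs of two kinds: delivery of the intervention (staff, training, materials) and "patient resource use in terms of the broader health service", the latter through the CSRI at baseline, 8 weeks and 6 months. One valuation method is described, for delivery: "The cost of providing the intervention will be calculated based on the average time taken to carry out the intervention", multiplied by a mid-scale hourly staff cost and raised for employer costs and overheads. Once that delivery cost has been estimated, "net cost benefit and cost-benefit ratio for providing the service will be calculated".

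On the comparison, the Design section says: "In the control condition, participants will receive TAU supplemented with a paper-based safety plan". Control Condition adds that these participants are oriented by the researcher and then make their plan with their clinician, who is encouraged to return to it over the same 8 weeks.

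**The concern.** A cost-outcome description sets costs beside outcomes in their natural units. A net benefit subtracts cost from benefit, and a cost-benefit ratio divides one by the other, so both require benefit and cost in the same unit, money. The section therefore commits to named statistics that do not belong to the evaluation it declares, and it does not say what the benefit is. Because this is a positive commitment to particular measures, it goes beyond detail that a condensed article leaves to a fuller plan.

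The cost side raises a second problem. The trial compares two ways of recording a safety plan. A benefit estimated between its arms is a benefit of app over paper, and the matching cost is the additional cost of app over paper. The section instead bases the measures on the delivery cost of the intervention, much of which is clinician time that the control arm also uses.

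At stake is what Objective 5 can conclude. A ratio with an undefined benefit and a mismatched cost would be hard to interpret, and it would come from a pilot that is not designed to establish an effect.

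**Working it through.** The article gives no cost, unit price, monetary benefit or ratio, so there is no stated figure to reproduce. The check takes each term the measures need, then the precision of the one available route.

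**1. Terms required.** Net benefit = B − C; cost-benefit ratio = B / C or its inverse, with B and C both in money.

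| Term | Data source stated? | Valuation stated? |
|---|---|---|
| Delivery cost of the intervention | Yes (Health Economics) | Yes: time × hourly cost, plus employer costs and overheads |
| Wider service use | Yes: CSRI, three time points, both arms | Not described |
| Monetary benefit B | Not defined | Not described |

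The measures in Research Question and Outcome Measure Feasibility are the BSSI, C-SSRS, CSES, INQ and CSRI. The first four are clinical or psychological scales. The CSRI records use of services. None is assigned a monetary value, so B is undefined as written.

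**2. The only route in the planned data.** CSRI contacts could be priced, and B taken as mean service cost in the control arm minus mean service cost in the app arm. This is a cost offset. It gives no value to changes in suicidal ideation, suicidal behavior or self-injury, which are the outcomes of interest.

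**3. Precision of that route.** Inputs: 80 randomized 1:1 and 25% dropout expected (Sample Size).

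- Completers: 80 × 0.75 = 60, or about 30 per arm.
- 95% half-width of a difference in means, equal SD in both arms, normal approximation: 1.96 × √(2/n) × SD.
- n = 30: 1.96 × √(2/30) = 1.96 × 0.258 = 0.506, about 0.51 SD of individual cost.
- n = 40 (no dropout): 1.96 × √(2/40) = 1.96 × 0.224 = 0.438, about 0.44 SD.

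Expressing this as a share of mean cost needs the ratio of SD to mean, which the article does not give. Purely as an illustration, ratios of 1 and 2 would give ±51% and ±101% of mean cost with 30 per arm. The conclusion does not rest on these two figures.

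**4. Cost basis.** Write S for delivery cost common to both arms, A for cost specific to the app and P for cost specific to the paper plan.

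- Delivery cost of the app arm: S + A.
- Cost that matches a between-arm benefit: (S + A) − (S + P) = A − P.

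S contains the clinician-led safety planning given in both arms (Control Condition, and the closing paragraph of Consent, where the arms are said to differ in how the plan is stored). The Clinicians section also has those delivering either arm complete the SafePlan training. SafePlan Condition says the app costs participants nothing. The article gives no values for S, A or P, so the gap between S + A and A − P cannot be sized. The two are equal only if S + P = 0, which the described control arm rules out.

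**The case against.** The strongest defence is that this is a condensed article. Unit costs for the CSRI and a definition of benefit could sit in a fuller plan, and averted service use is a recognizable monetary benefit. Part of that stands: the absence of CSRI unit costs is not an error. It does not remove the conflict between the declared evaluation and the promised measures, because both are stated in the same section.

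The defence can also say that the section fixes no comparator and does not say the paper arm will go uncosted. The Clinicians section speaks of the intervention as delivered in both arms, so the costed item might be safety planning in general. This softens the cost point but does not remove it. On that reading there is no arm without safety planning, so the trial offers no between-arm estimate of its benefit to set against the cost.

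On precision, it is fair that a pilot of this size estimates any mean difference loosely, including the difference recommended below. The half-width argues against a headline ratio; it does not argue against reporting costs.

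Three stronger readings are tempting, and the article does not support them:

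- A reader might infer that the trial costs only the intervention. It does not: wider service use is collected through the CSRI in both arms. Only the valuation method is confined to delivery.
- A reader might infer that the ratio cannot be computed at all. A partial cost-offset ratio could be. The accurate statement is that the measure is undefined as written.
- A reader might fault Table 1 for having no field for delivery time. That table schedules participant data, Health Economics separately says delivery resource use will be collected, and form-level detail is commonly left out of an article.

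**Conclusion.** The concern holds as an inconsistency that should be corrected. The section names one type of evaluation and promises the summary measures of another, leaves the monetary benefit undefined, and ties the measures to a cost that is not incremental between the arms. The only benefit obtainable from the planned data would leave the suicide outcomes unvalued and would carry a 95% half-width of about 0.51 SD of individual cost. That figure assumes the full 25% dropout, equal SDs in the arms and a normal approximation. Skewed costs would make the approximation rougher.

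The reach is limited. Economics is the last of five objectives, the primary outcomes are feasibility outcomes, and the sample size for a full trial is to come from the BSSI. Only the conclusion of Objective 5 changes.

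**What to change.** In Health Economics, delete the net cost benefit and the cost-benefit ratio. In their place, state that the cost-outcome description will report, by arm, mean delivery cost (orientation, clinician time, training, materials) and mean CSRI service cost. The app-minus-paper difference in cost and its 95% CI should be set beside the BSSI difference. Say explicitly that delivery resource use is recorded in the paper arm as well as the app arm. Word Objective 5 to match, as a cost-outcome description.

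The cost is small. It is a change of wording that uses data already planned. The one thing given up is a single summary ratio. If the sponsor prefers to keep a monetary summary, the section would have to define the benefit (for example, CSRI cost offsets) and how it is valued, use the incremental cost of app over paper, and state that the clinical outcomes are not valued. That is more work for a quantity this pilot would estimate poorly.

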#### Qualitative Data Analysis

Qualitative data from interviews with study participants and clinicians will be analyzed via thematic analysis using the approach by Braun and Clark [49]. Data collection will continue until data saturation is reached. In total, 25% (9/36) of the interviews will be double coded to ensure reliability. Disagreements will be resolved by discussion.

There are specific ethical challenges when conducting qualitative research. As there may be potential for distress, the team developed a research protocol that provides contact details of appropriate additional support if needed. It is important to maintain confidentiality and pseudoanonymity. Informed consent is an ongoing process that continues after obtaining written consent [50]. The team will be cognizant of this throughout the project.

McGrath and Nilsson [51] outlined the challenges in qualitative data sharing. However, transparency and rigor are critical. We will use some of the strategies outlined by McGrath and Nilsson [51], which include outlining procedures for data sharing when obtaining informed consent, data minimization, and pseudonymization.

Tsai et al [52] advocated that “coding queries may offer greater anonymity compared with full transcripts because statements are grouped by theme rather than by study participant.” They further support this process as preferable to sharing full transcripts. In this research, qualitative analysis will be managed using NVivo (version 12; QSR International) qualitative analysis software [53]. This will provide a clear audit trial and permit the execution of coding and matrix queries to ensure transparency.

### Progression From Feasibility to Full Trial

Shanyinde et al [54] reported 14 issues that needed to be evaluated in feasibility studies or pilot trials. “A process for Decision-making after Pilot and feasibility Trials” (ADePT) by Bugge and Williams [55] examines the “methodological issues” identified in a feasibility study that may hinder or facilitate progression to a definitive trial. ADePT permits an examination of the evidence from the feasibility study and the degree to which “methodological issues, ” such as recruitment, retention, adherence, and acceptability of the intervention, among others, have been successful. From the feasibility study findings, ADePT provides a framework to decide whether there should be an amendment to the intervention, context of its delivery, and confirmed trial design before embarking on a full trial. This study will use the ADePT 14-point reporting framework of methodological issues and decision tools to evaluate whether the feasibility study has achieved its objectives and to identify the need for intervention, clinical context, and trial design modification.

